### Statistical Analysis

#### Primary Analysis

The primary analysis will follow the intention-to-treat principle, meaning that all randomized participants will be analyzed according to their assigned groups regardless of intervention adherence, withdrawal, or protocol deviation. Between-group differences in SPIN scores at 1-month posttreatment and 3-month follow-up will be examined using linear mixed effects models. The model will include group, time, and the group-by-time interaction as fixed effects, baseline SPIN score as a covariate, and a participant-specific random intercept to account for repeated measurements. The data will be automatically generated by Google Forms once participants complete their responses. A *P* value of less than .05 will be used as the level of statistical significance.

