### Research Objectives and Hypotheses

Our aim is to test the preliminary efficacy of a therapist-facilitated VR intervention for reducing social anxiety symptoms among young individuals, compared with a waitlist control condition. The primary research question is: “Does the therapist-facilitated VR intervention, when compared to waitlist group, result in a reduction of social anxiety symptoms among youths at 1-month (post-treatment) and 3-month follow-up?” Additionally, the study aims to investigate the cost-effectiveness of this intervention by determining “What is the cost per unit reduction in the SPIN score (if applicable)?” The study does not aim to establish implementation effectiveness in routine service settings or definitive generalization to real-world behavior. Our hypotheses are as follows:

H1: Compared with the waitlist control, a therapist-facilitated VR intervention will reduce social anxiety symptoms at the 1-month (posttreatment) follow-up.H2: Compared with the waitlist control, a therapist-facilitated VR intervention will reduce social anxiety symptoms at the 3-month follow-up.H3: The VR intervention will demonstrate a cost per unit reduction in social anxiety symptoms, providing an estimate of its economic feasibility.

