### Recruitment

The trial will enroll 90 participants, allocating 45 to each arm. Allowing for 15% attrition, this sample provides 90% power to detect a treatment effect at T1, assuming an independent samples 2-tailed *t* test, an *α* level of .05, and Cohen *d* of 0.75. The target size also accords with comparable 2-arm VR intervention studies [16].

The first participant was enrolled in March 2026. The study will recruit participants from various settings in Hong Kong, including middle schools, tertiary institutions, and community centers. Adequate participant enrollment will be facilitated through partnerships with collaborating institutions, which will post digital flyers and promotional videos on their social-media platforms to reach the target population. The participants’ inclusion criteria were as follows: youth aged 15 to 25 years with a score of 25 or higher on the Social Phobia Inventory (SPIN). The exclusion criteria were as follows: (1) inability to attempt a baseline assessment (eg, due to being unpermitted to leave a psychiatric ward); (2) photosensitive epilepsy or significant visual, auditory, or balance impairment; (3) currently receiving another intensive psychological intervention; (4) a history of neurological conditions (eg, traumatic brain injury); and (5) insufficient language proficiency to understand the intervention requirements. In this trial, any endorsement of suicidal ideation will trigger crisis intervention procedures. Participants will be promptly flagged, and a trained clinician will notify the school or guardian to ensure appropriate safety measures are taken. School tutors or social workers familiar with students’ mental health will help identify participants unsuitable for the study, especially those whose conditions may be masked in self-report questionnaires. Participants will be recruited and screened online or offline, but will complete all interventions offline. Participants will be briefed through tutorial video clips demonstrating the research flow regarding intervention procedures, timing, and frequency.

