### Outcomes

Basic demographic and clinical data, including age, gender, region, and socioeconomic status, will be collected. The primary outcome will be the SPIN, while the secondary outcome will be the Patient Health Questionnaire-9 (PHQ-9) for depressive symptoms. All outcomes will be self-assessed using the following online measurements at baseline, 1-month (postintervention), and 3-month follow-up (Figure 4).

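### SPIN at 1 month and at 3 months stand as equal primary hypotheses at .05 with no decision rule, while the sample size rests on 1 month alone

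*Protocol article*

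**What the plan says.** All references are to the protocol article.

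- **Research Objectives and Hypotheses.** The primary question asks whether the intervention will "result in a reduction of social anxiety symptoms among youths at 1-month (post-treatment) and 3-month follow-up". It is then divided into H1, that "a therapist-facilitated VR intervention will reduce social anxiety symptoms at the 1-month (posttreatment) follow-up", and H2, that "a therapist-facilitated VR intervention will reduce social anxiety symptoms at the 3-month follow-up". Expected Findings, in the Discussion, repeats the hypothesis for both visits.
- **Outcomes.** The measure is named but no visit is singled out: "The primary outcome will be the SPIN, while the secondary outcome will be the Patient Health Questionnaire-9 (PHQ-9) for depressive symptoms".
- **Primary Analysis.** "Between-group differences in SPIN scores at 1-month posttreatment and 3-month follow-up will be examined using linear mixed effects models". The model includes "baseline SPIN score as a covariate, and a participant-specific random intercept to account for repeated measurements". On the criterion, a P "value of less than .05 will be used as the level of statistical significance".
- **Recruitment.** With 45 per arm, 15% attrition, a two-tailed t test at .05 and d=0.75, "this sample provides 90% power to detect a treatment effect at T1". No power is given for T2, or for T1 and T2 together.

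**The concern.** The objectives and the analysis section give the two visits equal primary standing. The sample-size section treats T1 as the visit that matters. Nothing in the article reconciles the two, so a result significant at only one visit has no agreed meaning in advance.

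Two success rules are possible, and the plan's figures fit neither. Under an either-visit rule there are two chances at .05, so the overall error rate is no longer .05. Under a both-visits rule the error rate is safe, but the 90% describes only one of the two hurdles. In practice, a trial with a significant difference at one visit and not at the other could be reported as positive on its primary outcome without the stated level or power supporting that claim.

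**Working it through.** **1. The plan's own figure.** Inputs from Recruitment: d=0.75, two-sided alpha .05, power 90%, attrition 15%.

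- n per arm = 2(1.960 + 1.282)² / 0.75² = 37.4, so 38 completers.
- 38 / 0.85 = 44.7, so 45 per arm and N=90. This matches.
- Power with 38 completers per arm: the noncentrality is 0.75 × √(38/2) = 3.269, which gives 90.5% (normal) or 89.7% (exact t). The 90% at T1 reproduces.

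**2. Two tests, each at .05.** Let Z1 and Z2 be the T1 and T2 test statistics with correlation r. The article does not give r, so a range is assumed. The only related figure is the SPIN test-retest correlation of 0.73 (Primary Outcomes: SPIN), which is not stated to be the T1–T2 correlation.

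- Two-sided error, either visit: P(|Z1|>1.96 or |Z2|>1.96) under no effect. At r=0 this is 1 − 0.95² = 9.75%.
- Error in favour of VR only: P(Z1>1.96 or Z2>1.96). At r=0 this is 1 − 0.975² = 4.94%, against 2.5% for a single test.
- Power for both visits: P(Z1>1.96 and Z2>1.96) with mean 3.269 for each, that is d=0.75 and 38 completers per arm at both visits. At r=0 this is 0.905² = 81.9%.

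| r (assumed) | Error, either visit | Favouring VR only | Power, both visits | Power, either visit |
|---|---|---|---|---|
| 0 | 9.75% | 4.94% | 81.9% | 99.1% |
| 0.5 | 9.07% | 4.54% | 84.0% | 97.0% |
| 0.73 | 8.20% | 4.10% | 85.6% | 95.4% |
| 0.8 | 7.81% | 3.90% | 86.3% | 94.7% |
| 0.9 | 7.04% | 3.52% | 87.5% | 93.5% |

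**3. A smaller effect at T2 (assumed values, not in the article).** Over r=0 to 0.9, power for both visits is 67% to 74% if d=0.60 at T2, and 53% to 59% if d=0.50.

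**4. The planned baseline-adjusted model.** Assume equal correlation ρ between any two visits, and d=0.75 on the raw SD at both follow-ups. Adjustment raises the effective d to 0.75/√(1−ρ²). The correlation between the two tests becomes (ρ−ρ²)/(1−ρ²) = ρ/(1+ρ).

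| ρ (assumed) | Effective d | r between tests | Error, either visit | Power, both visits |
|---|---|---|---|---|
| 0.3 | 0.786 | 0.231 | 9.6% | 87% |
| 0.4 | 0.818 | 0.286 | 9.5% | 90% |
| 0.5 | 0.866 | 0.333 | 9.5% | 94% |
| 0.73 | 1.097 | 0.422 | 9.3% | 99.5% |

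Adjustment therefore moves the either-visit error towards the upper end of the range, while it can remove the shortfall in joint power.

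**The case against.** The strongest reply has four parts.

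- **It is a matter for the analysis plan.** A condensed article may leave the order of testing to a document not shown here, and the article states no either-visit rule. This stands in part: such a plan could supply an order. But the article itself fixes the primary question, two hypotheses, two primary contrasts and one level, and these do not agree with its own sample-size basis.
- **The only power claim is correct.** This stands. A reader might infer that the 90% is wrong or that a promised joint power is missed. The article promises power at T1 only, and that figure reproduces. The accurate statement is that no power is given for T2 or for both visits.
- **The figures depend on assumptions.** This stands. A rate of 8% to 9% holds only for r of about 0.53 to 0.77. H1 and H2 are directional, and counting only false results favouring VR gives about 3.5% to 4.9%, against 2.5% for one test. The joint-power shortfall is not certain under the adjusted model.
- **The trial calls itself preliminary.** This lowers the severity but does not settle the question, because the article still sets hypotheses, a significance level and a power target, and will report efficacy against them.

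**Conclusion.** The point holds at moderate severity. T1 and T2 have equal primary standing at .05 with no order, split or success rule, and the sample size covers T1 alone.

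- **Either visit suffices:** the two-sided error is about 7% to 9.75% for r from 0.9 to 0. Power is not lost.
- **Both visits required:** the error rate is not inflated. Joint power is about 82% to 87.5% on the article's t-test basis, with d=0.75 and 38 completers per arm at both visits, and lower if the T2 effect is smaller. Baseline adjustment could restore about 90% if visit correlations reach about 0.4 and the T2 effect equals that at T1.

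A reader might infer that the trial suffers both harms at once. It cannot: they belong to alternative rules, and the article does not say which applies. That silence is the defect.

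**What to change.** Amend Research Objectives and Hypotheses and Primary Analysis along these lines:

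> The single primary endpoint is the between-group difference in SPIN at T1, tested two-sided at .05. The difference at T2 (H2) is tested at .05 only if the T1 test is significant. Otherwise T2 is reported as an estimate with its 95% confidence interval.

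This follows the visit on which the sample size was built, holds the error rate across both tests at .05, and leaves N=90 and the power at T1 unchanged. The cost is that no confirmatory claim at T2 is possible if T1 fails. Splitting alpha equally (.025 each) would be dearer: unadjusted power at T1 falls to 83% (exact t) or 85% (normal), and 90% would need 46 completers per arm instead of 38.

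Enrolment began in March 2026, so this is a change to a running trial and must be dated and justified. It should be made before unblinding, and preferably before any comparison of the coded groups, because masked labels do not hide which visit reached significance.

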## Methods

### Trial Design

The design is a 2-arm, statistician-blind, parallel-group RCT to test whether the VR intervention, compared with a waitlist control condition, leads to a reduction in social anxiety among youth. Assessments will be carried out at 0 (baseline, T0), 1 (posttreatment, T1), and 3 (follow-up, T2) months. A summary of the trial design can be seen in Figure 1.

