#### Primary Outcomes: SPIN

Developed by Connor et al [22], SPIN is a brief self-report tool consisting of 17 items that assess fear, avoidance, and physiological discomfort in social situations. It is specifically designed for use with social anxiety disorder [23]. The Chinese version of the SPIN has been examined with good internal consistency (Cronbach *α*=0.85) and test-retest reliability (*r*=0.73). A cutoff value of 25 or higher has demonstrated strong reliability and validity and is commonly used to screen for social anxiety in the Chinese population [24].

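### The random-intercept primary model, with the usual equal-variance residual, assumes one SPIN variance at T1 and T2; if these differ, one of H1 and H2 is tested above 5% and the other below.

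*Protocol article*

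**What the plan says.** Under Trial Design: "Assessments will be carried out at 0 (baseline, T0), 1 (posttreatment, T1), and 3 (follow-up, T2) months".

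Under Primary Analysis, the targets are two visit-specific contrasts: "Between-group differences in SPIN scores at 1-month posttreatment and 3-month follow-up will be examined using linear mixed effects models". They correspond to H1 (1 month) and H2 (3 months) in the objectives, and the significance threshold is .05. The mean structure is given as "The model will include group, time, and the group-by-time interaction as fixed effects", and the remaining terms as "baseline SPIN score as a covariate, and a participant-specific random intercept to account for repeated measurements". The section mentions no visit-specific residual variance, no robust standard error and no baseline-by-time term. The Secondary Analyses section carries a similar model over to the PHQ-9.

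The Recruitment section plans 90 participants in two equal arms and states: "Allowing for 15% attrition, this sample provides 90% power to detect a treatment effect at T1". The calculation behind this is a two-sided t test comparing two groups at the 5% level with d = 0.75.

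The SPIN section reports a test-retest correlation of 0.73 for the Chinese version, without the retest interval. The protocol gives no SPIN standard deviation at any visit.

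**The concern.** Baseline SPIN is a covariate and the targets are the differences at T1 and T2, so the natural reading is two outcome rows per participant. A random intercept with independent, equal-variance residuals is then compound symmetry. The two visits share one variance, so with complete data the T1 and T2 contrasts get the same standard error. The single baseline slope likewise cannot differ between visits.

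The trial reads the two contrasts as separate hypotheses, so each needs a standard error that is right for its own visit. The visits lie 1 and 3 months after baseline, one directly after treatment and one at follow-up, and nothing in the protocol suggests that the adjusted variance is the same at both. At stake is the error rate of each test and the coverage of each interval. With complete data the estimated differences themselves are not biased.

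**Working it through.** **1. The plan's own figure.** 45 × 0.85 = 38.25, so about 38 per arm. With d = 0.75 and two-sided α = .05, the noncentrality is 0.75 × √(38/2) = 3.27. Power is 90.5% by the normal approximation and 89.7% by the noncentral t. In reverse, 38 per arm / 0.85 gives 45 per arm and 90 in total. The stated 90% reproduces.

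**2. Effect of pooling.** Let v1 and v2 be the baseline-adjusted SPIN variances at T1 and T2. With equal arms and complete data, the model's standard error at visit k divided by the true one is √[((v1 + v2)/2) / vk]. Coverage of a nominal 95% interval is 2Φ(1.96 × ratio) − 1. The variance ratio is an assumption, so both directions are shown.

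| v2/v1 | SE ratio T1 | SE ratio T2 | Coverage T1 | Coverage T2 |
|---|---|---|---|---|
| 0.5 | 0.866 | 1.225 | 91.0% | 98.4% |
| 0.67 | 0.914 | 1.116 | 92.7% | 97.1% |
| 0.8 | 0.949 | 1.061 | 93.7% | 96.2% |
| 1.0 | 1.000 | 1.000 | 95.0% | 95.0% |
| 1.25 | 1.061 | 0.949 | 96.2% | 93.7% |
| 1.5 | 1.118 | 0.913 | 97.2% | 92.6% |
| 2.0 | 1.225 | 0.866 | 98.4% | 91.0% |

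The true test level is 100% minus coverage. At a ratio of 1.5 it is 2.8% at T1 and 7.4% at T2.

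**3. Check by simulation.** REML random-intercept fits, 38 per arm, 250 replicates per scenario, assumed residual correlation 0.6:

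- Variances 1 and 1: model SE 0.229 at both visits, empirical 0.231 at both; coverage 95.2% and 95.2%.
- Variances 1 (T1) and 1.5 (T2): model SE 0.258 at both, empirical 0.223 and 0.294; coverage 98.0% and 91.2%.
- Variances 1.5 (T1) and 1 (T2): model SE 0.257 at both, empirical 0.266 and 0.236; coverage 93.2% and 98.8%.

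With 250 replicates, the Monte Carlo error of a coverage near 95% is about √(0.95 × 0.05/250) = 1.4 points.

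**4. What variance ratio might arise.** If the total SPIN variance is equal at both visits, vk is proportional to 1 − rk², where rk is the correlation of visit k with baseline. Take r1 = 0.73, borrowing the test-retest value, and let r2 be assumed:

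- r2 = 0.65: v1 = 0.4671, v2 = 0.5775, ratio 1.24. SE ratios 1.057 and 0.951; levels 3.8% and 6.2%.
- r2 = 0.40: v2 = 0.84, ratio 1.80. SE ratios 1.183 and 0.882; levels 2.0% and 8.4%.

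With weaker correlations, 0.50 and 0.40, the ratio is only 0.84/0.75 = 1.12 and the levels are 4.4% and 5.7%.

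**5. Does the alternative repair it?** Simulated null rejection at T1/T2, with 90 randomised, 15% lost and 1,500 runs:

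- Correlations 0.73/0.50: random intercept 2.2%/7.7%; unstructured covariance with baseline-by-time 4.5%/5.3%.
- Correlations 0.73/0.73: 5.3%/4.9% and 5.1%/4.9%, so the two models agree.

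**6. Power at the planned effect.** With 38.25 per arm, r1 = 0.73 and r2 = 0.50, the true T1 standard error in SD units is √(2/38.25 × 0.4671) = 0.156, and 0.75/0.156 = 4.80. Power is Φ(4.80 − 1.96) = 99.8% with the correct standard error. With the pooled one it is Φ(4.80 − 1.96 × 1.141) = 99.5%. At r2 = 0.40 it is 99.3%.

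**The case against.** **No basis for a direction.** A reader might infer that the T1 interval is bound to be too wide and the T2 interval too narrow, because scores drift from baseline with time. The documents do not support this. They give no SPIN variance at either visit and no correlation of T2 with baseline. The 0.73 is a reliability figure with no stated interval and need not apply across a treatment period. If participants differ most in their response right after treatment, T1 could be the more variable visit, and then it is T1 that is tested above 5%. This objection stands, so the point is made without a direction.

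**Loss of planned power.** A reader might also infer that the T1 power is at risk. At a smaller effect of d = 0.5 with correlations 0.73/0.50, simulated T1 power was 78.5% against 87.0%, and a separate run gave 84.5% against 89.7%. The trial is sized at d = 0.75 on an unadjusted t test, and there the difference is negligible under these correlations. This objection stands too.

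**Silence on the residual.** The article states no residual structure, and an analysis plan not shown could add visit-specific variances to the random intercept. This stands in part, which is why the point is conditional on the usual residual. The article does, however, name the random intercept as the device for handling the repeated measurements, so the choice is not simply left open.

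**A common model with a modest effect.** This is true. Coverage stays between about 91% and 98% even at a twofold variance difference. It argues for low weight, not for keeping an assumption that costs almost nothing to drop.

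**Conclusion.** The point holds in conditional form. Fitted with the usual residual, the stated model assumes equal baseline-adjusted SPIN variances at T1 and T2. If they are unequal, one of H1 and H2 is tested above 5% and the other below, and which one cannot be told from the protocol. The higher level is about 6.3% at a variance ratio of 1.25 (in either direction), 7.4% at 1.5 and 9.0% at 2.0. Equal variances give no error.

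This rests on baseline entering only as a covariate; if T0 were also an outcome row, three visits would be pooled and the pattern could differ. The table also assumes complete data and equal arms. The sample-size statement is unaffected. This is a worthwhile low-cost improvement to the primary model, not a flaw that invalidates it.

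**What to change.** In the Primary Analysis section, replace the participant random intercept with an unstructured 2×2 residual covariance over T1 and T2, fitted by REML with Kenward-Roger degrees of freedom. Add a baseline SPIN-by-time term, and keep the T1 and T2 group contrasts as they are. Use the same structure for the PHQ-9 under Secondary Analyses.

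The cost is one extra covariance parameter, one extra fixed effect and a sentence of text. It needs no new data and no change to the sample size. In the simulations nothing was lost when the variances were equal. The change should be made while the statistician is still blinded.

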#### Secondary Analyses

A similar linear mixed effects modeling approach will be used for secondary outcomes, including depressive symptoms measured by the PHQ-9. Exploratory analyses will examine adherence indicators, including the number of sessions attended, task completion, and homework completion. Where appropriate, adherence may be examined as a predictor or moderator of symptom change. Physiological indicators, including HRV and EDA, will be analyzed descriptively and, where data quality permits, using repeated-measures models to explore within-participant changes across sessions and associations with subjective outcomes.

#### Covariates and Potential Confounding Variables

Selected baseline variables will be included in the final analyses to improve precision. These may include age, gender, baseline social anxiety severity, baseline depressive symptoms, recruitment setting, and prior or concurrent mental health support.

#### Missing Data and Dropout-Related Bias

Linear mixed effects models can accommodate missing outcome data under the missing-at-random assumption. Patterns of missingness and dropout will be examined descriptively by group. If missing data are substantial, multiple imputation or other sensitivity analyses will be conducted to assess the robustness of the findings.

#### Cost Analysis

The cost analysis will encompass the following components: (1) personnel costs, including expenses for the training and recruitment of mental health professionals; (2) VR equipment and software costs, such as VR headsets and software licenses; and (3) materials and supplies (eg, office supplies, printing, and miscellaneous). The total cost will be divided by the average reduction in SPIN scores to calculate the cost per unit reduction in SPIN score.

### Dissemination Plan

Findings will be disseminated through peer-reviewed publications, academic conferences, and knowledge exchange activities with collaborating schools, community organizations, and youth mental health stakeholders. Nontechnical summaries will be prepared for service providers and community partners to support future intervention refinement and implementation planning.

